**Figure 1 F1:**
[figure not shown]
Flow diagram for the study.

The study is estimated to take about 12 months: 4 months to recruit participants and 8 months for participant follow-up. The study will be carried out in 16 Treatment and Diagnostic Centres in Yaoundé (the capital of Cameroon).

### Participants and inclusion and exclusion criteria

Participants eligible for this study must be newly diagnosed with TPM + and aged at least 18 years (born before 1 January 1995). The usual diagnostic procedure of the PNLT will be followed, which is that all patients with clinical signs of pulmonary tuberculosis will undergo two smear tests in the laboratory selected for the study. At least one of these tests must be positive. In addition, the patient must know how to read French or English, have a mobile phone for personal use, know how to open and read an SMS on a telephone and give consent (signed on the informed consent form) after having been informed about the goals, the process and the expected results of the study. Hospitalised patients or severely ill patients, as identified by health staff, will be excluded.

### Cure status

A participant is considered to be:

•Cured, if they have a negative smear test after 6 months of treatment.

•Not cured or a treatment failure if they have a positive smear test after 5 months of treatment.

•Transferred, if they are referred to continue treatment in another Treatment and Diagnostic Centre out of the study zone.

•Dead, if they die between the screening phase and the end of treatment, regardless of the cause of death.

•Lost to follow-up, if they receive at least one month of treatment and are not in any of the classes above.

### Implementation of the study

All participants in the study will receive usual care from the National Programme for the Fight against Tuberculosis. Free tuberculosis treatment lasts for an intensive phase (quadri-therapy for the first two months) followed by a continuation phase (bi-therapy from the third to the sixth month). Participants attend appointments to receive supplies of the drugs (once a week or month for the first two months then once a month between the third and sixth months) and follow-up of treatment adherence. Participants undergo a smear control test at the end of the second, fifth and sixth months. Finally, participants receive education and counselling.

After a preliminary interaction with health staff in the various centres on the importance of the study, all participants (in the two groups, control and intervention) will receive a message of welcome, then a phone call from the secretary of the study to check that the phone number actually belongs to the participant, and to confirm inclusion in the study.

#### Intervention group

The participants in the intervention group (SMS intervention) will receive daily SMS reminders in French or English. These messages will aim at reminding, inciting or motivating them to take their prescribed tuberculosis drugs. To maintain their attention and interest, these messages will be changed every two weeks (for example, ‘Good morning, it is important to take your drugs against TB every day’ , ‘Good morning, taking drugs daily increases your chance of healing’ , and so on). Additional encouraging messages will also be sent every 2 weeks (for example, ‘Congratulations! The first month of treatment is over’ , and so on). Messages are neutral and similar for both sexes. During each clinical follow-up (a visit at health centre), problems (such as side effects of drugs, problems with adherence to treatment and SMS reception) as well as solutions will be recorded by health staff in the participant’s health records and by the secretary in the daily log. Participants will also receive messages at the end of treatment to thank them for participating in the study.

#### Control group

Participants in the control group will only receive a welcome message at the beginning, to validate their entry into the study, and a message at the end of treatment to thank them for their participation. These participants will not receive daily SMS reminders.

### Outcomes and plan for analysis

#### Primary outcome

The primary objective (Table 1) is to measure the difference in cure rate at 6 months between the SMS intervention group and control group.

**Table 1 T1:** Outcomes of the study

**Outcomes**	**Measure of outcomes**	**Type**	**Statistical analysis**
**Primary**			
**Cure**	**Percentage of cured patients**		
Bacilloscopy (second, fifth, sixth months)	Percentage of patients with positive or negative bacilloscopy results	Categorical	Chi-square
Cure (sixth month)	Percentage of cured patients	Binary	Chi-square
			Logistic regression
**Secondary**			
**Adherence of patients to treatment (second, fifth, sixth months)**			
Drug prescriptions collected and doses taken (visual analogue scale)	Percentage of adherence to treatment during the last 30 days	Continuous	*t*-test
Keeping appointments		Binary	Chi-square
Punctuality of appointments		Categorical	Chi-square
**Multi-drug-resistant tuberculosis (fifth and sixth months)**	Percentage of patients with multi-drug-resistant tuberculosis	Binary	Chi-square
**Satisfaction (sixth month)**	Satisfaction	Continuous	*t*-test

The status of each patient will be based on the results of smear tests carried out in the second, fifth and sixth months in the treatment centre. At the fifth month, two scenarios are possible. If the smear test is negative, treatment continues during the sixth month. At 6 months, the final smear test is done to see if the patient is cured. If this test is negative, the patient is classified as cured.

If the test at 5 months is positive, a second smear test will be performed to confirm the result (which is not mandatory for this study). At this moment, the patient will be considered as a treatment failure and classified as not cured in the study.

Participants lost to follow-up or referred to other treatment centres, will be considered cured (best case) or not cured (worse case) as two extreme statistical scenarios.

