## Background

As in many other countries in the world, tuberculosis is a major public health problem in Cameroon. In 2010, there were 24,528 cases of tuberculosis (all forms included) with a prevalence rate of 122 per 100,000 inhabitants [1]. The number of new sputum positive cases in the country was 14,464 in 2010 [1]. With an estimated HIV prevalence rate of 5.3% [2], the rate of co-infection was estimated at 33% in new cases of sputum positive pulmonary tuberculosis (TPM+) [1].

In accordance with international directives (Directly Observed Treatment Short, DOTS [3] and the Global Strategy and Plan to Stop TB [4,5]), Cameroon has established the National Tuberculosis Control Programme (PNLT) for the fight against tuberculosis, financed by the state and international funding partners such as the Global Fund. This national programme aims to elaborate on and execute the National Policy in the fight against tuberculosis [1]. However, the DOTS strategy is often not well applied because its implementation, especially in developing countries, is complex [6], has numerous barriers [7] and needs enormous resources [8]. This is why there are many adaptations (Partially Observed) depending on the context. In the treatment of tuberculosis in Cameroon, for instance, during the intensive phase of treatment (the first two months), instead of receiving daily observable drug doses, a patient receives several doses weekly or monthly. In the continuation phase (from the third to the six month) they receive these doses monthly.

Irregular adherence to tuberculosis treatment causes therapeutic failure, leads to prolonged periods of infectiousness [9], provokes relapses [10], favours the emergence of drug resistance [11,12], requires prolonged and expensive treatment schemes, which do not guarantee effectiveness [13], and finally, increases morbidity and mortality [9].

The therapeutic success rate is the proportion of cases that complete 6 months of treatment and where a sputum test carried out at 5 months finds no Koch’s bacilli (KB). The cure rate is the proportion of cases that complete 6 months of treatment and where a sputum test carried out at 6 months finds no KB. In Cameroon, the therapeutic success rate is around 77% [2], while the cure rate is around 65% [2], which is 20% below the objective fixed by the PNLT. This low cure rate may be due to several causes.

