### Sample size

Presently, the cure rate for tuberculosis with the DOTS strategy is around 65% [2] in Cameroon, about 20% lower than the objective fixed by PNLT. Our hypothesis is that the cure rate in the SMS intervention group will reach 85%. For an attribution ratio of 1:1 in the two groups, 80% power, an alpha error of 5% and a two-sided test (effects may be interpreted independent of the way they go), we require a sample size of at least 166 participants [39], 83 in the SMS intervention group and 83 in the control group. Considering that the risk of loss to follow-up at the end of the study is important, we increased the sample size by 20%, giving 199 participants. Also, for the urban zone, we estimated that at least 90% of eligible people will have mobile phones and that at least 80% of them will consent to take part. The total number of eligible participants was therefore increased by 10% and another 20%, leading to a total of 260 participants.

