### Plan for data analysis

The results of this study will be reported following CONSORT standards [40] on randomized trials. A data entry mask developed using the Epi Data Entry program by the main investigator will be used to enter and control the quality of patient data. Analysis of the primary outcome will use the intention-to-treat approach, which includes all participants in their initial study group allocation. All participants for which there are no smear test results at 6 months will be considered not cured or cured (worst case or best case scenario). Results will be presented depending on the type of variable: means (± standard deviation) and medians (minimum and maximum) for continuous variables and percentages for categorical or binary variables.

The two groups will be described according to their baseline characteristics. Student’s test (*t*-test) will be used to calculate the difference between the two groups for continuous variables while the chi-square test will be used for categorical or binary variables. The association between study groups and cure rate will be analysed using a logistic regression model reporting the odds ratio and 95% CI.

Each individual characteristic, such as age, sex, level of education, socio-economic category, and HIV status, will be tested for an association with the cure status in a univariate analysis of the control group. Each characteristic that is significantly related with the outcome (*P* < 0.1) will be tested using a bivariate model that includes the study group, cure status and the potential confounder. If introducing the variable changes the odds ratio by more than 10%, then the variable will be considered as a potential confounder of the association and will be used in the final multivariate model.

The data from this study will be analysed using the SPSS programme (v21.0) or STATA (v11). Comparisons between the two groups will be expressed in terms of the odds ratio and the number needed to treat. Open questions in the questionnaire (especially problems observed during follow-up) will be analysed using the content analysis technique.

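### The primary intention-to-treat analysis carries two opposite missing-outcome rules, names neither as primary, and gives no rule for when they disagree

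*Protocol article*

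**What the plan says.** The rule appears twice in the protocol article.

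- Under *Primary outcome* (the text after Table 1), participants who are lost or referred to another centre "will be considered cured (best case) or not cured (worse case) as two extreme statistical scenarios".
- Under *Plan for data analysis*, directly after intention-to-treat is stated for the primary outcome, all participants without a 6-month smear result "will be considered not cured or cured (worst case or best case scenario").

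The two statements differ in scope: the first covers losses and transfers, the second anyone lacking a 6-month smear. Neither distinguishes the arms, labels one scenario as the main analysis, or says how to conclude if they differ.

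The endpoint is defined in *Background*: "The cure rate is the proportion of cases that complete 6 months of treatment and where a sputum test carried out at 6 months" is free of bacilli. The same source is cited there for the 65% cure rate and again in *Sample size*, where "the cure rate for tuberculosis with the DOTS strategy is around 65"%. *Cure status* requires a negative smear after 6 months for cure. It treats a positive smear at 5 months as not cured, and lists transferred, dead and lost as separate classes.

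**The concern.** An intention-to-treat comparison of all randomised participants cannot be computed without one value for each missing outcome. The article offers two opposite values, so it defines two primary analyses. This goes beyond detail left for an analysis plan, because the article itself fixes the rule and fixes it as an unresolved alternative.

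The choice matters because the intervention is meant to improve adherence and may also affect retention. If control participants are lost more often, counting losses as cured credits the control arm for them. Counting losses as not cured turns the difference in loss into a difference in cure.

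The cured rule has a further problem. Read literally, the wording in *Plan for data analysis* would count as cured a participant who died, or who failed at month 5 and had no month-6 smear. *Cure status* and *Primary outcome* classify these participants as dead or not cured.

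**Working it through.** **Inputs from the article.** Cure 65% (control) and 85% (SMS); "80% power, an alpha error of 5% and a two-sided test"; 1:1 allocation; a 20% allowance for loss (*Sample size*); 288 included (*Trial status*), taken as 144 per arm. The article gives no split of losses by arm, so every split below is an assumption. P-values are Pearson chi-square without continuity correction.

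**The plan's own figure.** With mean rate 0.75, n per arm = [1.96√(2×0.75×0.25) + 0.842√(0.65×0.35 + 0.85×0.15)]² / 0.20² = 72.4, or 73. With the continuity correction this becomes 82.1, or 83. The stated 166 (83 + 83) is reproduced.

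**Can the rules disagree?** Take 144 per arm. SMS: 122 cured, 11 lost. Control: 94 cured, 36 lost.

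| Rule | SMS | Control | Difference | p |
|---|---|---|---|---|
| Lost = not cured | 122/144 = 84.7% | 94/144 = 65.3% | +19.4 points | 0.0001 |
| Lost = cured | 133/144 = 92.4% | 130/144 = 90.3% | +2.1 points | 0.53 |

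A borderline example with a smaller imbalance is SMS 95 cured, 20 lost, and control 78 cured, 38 lost. The not-cured rule gives +11.8 points (p=0.041, or 0.054 with Yates' correction). The cured rule gives -0.7 points (p=0.88).

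**When do they agree?** Apply 85% and 65% to those observed, at 144 per arm, using expected counts:

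| Loss, SMS / control | Lost = not cured | Lost = cured |
|---|---|---|
| 20% / 20% | 98 vs 75, p=0.006 | 127 vs 104, p=0.0007 |
| 15% / 25% | 104 vs 70, p<0.0001 | 126 vs 106, p=0.003 |
| 10% / 30% | 110 vs 66, p<0.0001 | 124 vs 109, p=0.025 |

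Both rules are significant in every row. These are expected counts. In 200,000 simulated trials with 20% loss per arm and the same rates, sampling variation still made the rules disagree in 18.7%. With 75% cure among those observed in both arms and 20% loss in each, at least one rule was significant in 8.6%, against a nominal 5%.

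**Do the two scenarios bound the difference?** Let m be the loss in each arm, and pI and pC the cure rates among those observed.

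- Both not cured: (1-m)pI - (1-m)pC = (1-m)(pI - pC).
- Both cured: [(1-m)pI + m] - [(1-m)pC + m] = (1-m)(pI - pC), the same value.
- SMS lost not cured, control lost cured: (1-m)(pI - pC) - m.
- SMS lost cured, control lost not cured: (1-m)(pI - pC) + m.

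With m = 29/144, 98 SMS cures and 75 control cures, both stated scenarios give 23/144 = +16.0 points. The opposed scenarios give (98 - 104)/144 = -4.2 and (127 - 75)/144 = +36.1 points.

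**Power if lost = not cured is primary.** If 85% and 65% hold only among those observed and 20% are lost per arm, the rates become 0.80×0.85 = 0.68 and 0.80×0.65 = 0.52. At 144 per arm, z = [0.16 - 1.96√(2×0.60×0.40/144)] / √[(0.68×0.32 + 0.52×0.48)/144] = (0.160 - 0.113)/0.057 = 0.82, which is power of about 79%.

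**The case against.** Four replies have force.

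1. **Both scenarios are stated in advance.** They read most naturally as a pair to be reported together. A reader might infer that the authors are free to pick the favourable one after seeing the data; the text does not say that. What stands is narrower: nothing decides the hypothesis when the two differ.
2. **The first illustration is unfavourable by construction.** Among those followed up, cure is 122/133 = 91.7% against 94/108 = 87.0% (p=0.23), so most of the contrast is the loss itself. A reader might infer that conflict is to be expected. At the planned rates among those observed, both rules stay significant at the expected counts even with 10% against 30% lost.
3. **The article never claims to bound the between-arm difference.** Scoring all losses one way, then the other, does bound each arm's cure rate. It remains true that agreement between the two scenarios says little about how robust the difference is.
4. ***Cure status* does not equate lost or transferred with not cured.** It lists them separately. Support for the not-cured rule comes from the *Background* definition, and for transfers it remains an imputation.

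A reader might also infer several co-primary tests, because Table 1 places "Bacilloscopy (second, fifth, sixth months") under its primary heading beside cure. The documents do not support this. The primary objective, primary hypothesis, primary outcome text and sample size all name cure as the single endpoint, and *Primary outcome* explains that these smears determine cure status.

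**Conclusion.** The point holds. The primary analysis is fixed as two opposite rules with no order between them, and the cured rule does not fit the definition behind the 65% planning rate. Taken literally, it also contradicts how the article classifies deaths and month-5 failures.

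The consequence is conditional. Opposite conclusions need unequal losses or a borderline result. The contrast of p=0.0001 with p=0.53 rests on assumed losses of 11 and 36 out of 144. With equal loss, the risk difference is identical under both rules and only the p-value moves.

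The result on bounds (+16 points under both rules, against about -4 to +36) assumes 20% loss in each arm, 85% and 65% among those observed, and the same value imputed in both arms. That last assumption is the plain reading, since no arm-specific assignment is mentioned.

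**What to change.** Before outcomes are compared by arm:

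- Name one primary analysis: cure at month 6 in all randomised participants, with anyone lacking a documented negative month-6 smear counted as not cured. This matches the *Background* definition.
- Keep lost or transferred = cured as a sensitivity analysis, with deaths and month-5 failures always counted as not cured. Align the wording of *Primary outcome*, *Plan for data analysis* and *Cure status* accordingly.
- Add the two arm-opposed scenarios (SMS missing not cured with control missing cured, and the reverse) as the true bounds on the difference.

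The cost is wording and extra tables, with no new participants or data. There are two downsides. Transferred participants who were cured elsewhere count as not cured. Power also falls if the 65% and 85% rates apply only to those observed, to about 79% at 144 per arm with 20% loss.

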#### Secondary outcomes

Firstly, we will measure the impact of SMS reminders on treatment adherence (regularity in collecting prescriptions and the percentage of prescribed doses taken; Table 1). Treatment adherence will be estimated by patient self-evaluation (indirect method) based on the visual analogue scale (VAS) during follow-up visits at 2, 5 and 6 months. Used in several studies [20,34-37], VAS measures the adherence of patients to treatment and correlates with results obtained from more objective methods such as electronic follow-ups [38]. Treatment adherence will be assessed by asking the patients to estimate their adherence to treatment on a 0 to 100% scale during the last 30 days before an appointment. This will give an adherence score and will be recorded three times (at the second, fifth and sixth months) by health staff responsible for the follow-up of these patients. We intend to use the average of the three values as a continuous variable to reflect patient global adherence to treatment. Further, our analysis will try to determine whether good adherence improves the cure rate.

Secondly, we will evaluate how well participants keep appointments at the second, fifth and sixth months. We will use a binary variable: ‘yes’ for patients who come between 4 days before and 4 days after the appointment date and ‘no’ for those who do not. We will use a categorical variable: ‘early’ for participants who come more than 4 days before the appointment date, ‘prompt’ for participants who come between 4 days before and 4 days after the appointment date and ‘late’ for participants who come more than 4 days after the appointment date.

Thirdly, we will estimate and compare the number of treatment failures due to resistance to tuberculosis drugs between the two groups. The laboratory test (resistance to rifampicin as measured using Genexpert [33]) will be conducted after the fifth month for defaulters by the PNLT. This variable will be analysed as a binary variable.

Finally, we will compare the degree of satisfaction for the two groups at the third appointment (at the end of 6 months). This assessment of the degree of satisfaction will be made by health staff involved in the care of participants using a questionnaire.

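### The three-visit VAS average and its t-test make the adherence comparison depend on retention to month 6, and the adherence–cure analysis is restricted in the same way

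*Protocol article*

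**What the plan says.** Under Secondary outcomes, the protocol article has patients rate their adherence "on a 0 to 100% scale during the last 30 days before an appointment". The score is "recorded three times (at the second, fifth and sixth months) by health staff responsible for the follow-up of these patients". The summary is then fixed: "We intend to use the average of the three values as a continuous variable to reflect patient global adherence to treatment". The next sentence adds a second use: "Further, our analysis will try to determine whether good adherence improves the cure rate". Table 1 lists VAS adherence at months 2, 5 and 6 as a continuous variable analysed by t-test.

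Under Cure status, a participant is "Cured, if they have a negative smear test after 6 months of treatment". Transfer, death and loss to follow-up are separate classes. The text after Table 1 deals with a positive month-5 smear: "At this moment, the patient will be considered as a treatment failure and classified as not cured in the study".

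The Plan for data analysis states intention-to-treat for the primary outcome. Its best-case and worst-case rule covers missing month-6 smear results only. Neither is extended to VAS.

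**The concern.** A VAS score exists only where a visit took place. The plan reduces three such scores to one number per patient, and there are two ways to do that when a visit is missing.

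- **All three values required.** Participants who die, transfer or are lost before month 6 have no summary and leave the t-test.
- **Available values averaged.** A patient who stops treatment in month 3 keeps the month-2 score as the measure of global adherence. The stopping itself is not counted.

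Either way, abandoning treatment, the most severe form of non-adherence, leaves no trace in the VAS measure. The trial's rationale is that poor adherence drives the low cure rate, so loss is unlikely to be unrelated to adherence. If reminders also keep patients in care, loss will differ by arm, and the groups compared are then no longer the randomised groups.

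The adherence–cure analysis meets the same problem. Staying to month 6 is needed to be classed as cured on an observed smear, so restricting to patients with a full average removes many of the not-cured.

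**Working it through.** **1. The plan's own figures.** No standard deviation or effect size is given for VAS. The relevant stated figure is the allowance for loss, in Sample size. For 65% vs 85%, two-sided 5% and 80% power, the pooled-variance formula gives

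n = [1.96·√(2·0.75·0.25) + 0.8416·√(0.65·0.35 + 0.85·0.15)]² / 0.20² = 72.4, so 73 per arm.

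With continuity correction this becomes 83 per arm, 166 in total, as stated. Then 166 × 1.2 = 199.2, which matches the stated 199. The plan therefore expects loss of about 20%. The Background section gives a programme success rate (treatment completed and month-5 smear negative) of about 77%. If controls resemble the programme, up to 23% would not meet both conditions.

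**2. Who has a three-value average.** Trial status reports 288 included.

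- 10% loss: 288 × 0.90 = 259
- 20% loss: 288 × 0.80 = 230
- 30% loss: 288 × 0.70 = 202

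**3. What an available-value average covers.** Each score refers to 30 days. Three visits describe 3 × 30 = 90 days of a course of about 180. A patient seen only at month 2 is described by 30 days, all in the intensive phase. Patients with different visit patterns are then compared on different periods.

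**4. Effect on the arm difference if complete cases are used.** This is an illustrative simulation, and none of its inputs is in the documents. Underlying adherence has mean 78 (control) and 85 (SMS) with SD 15. Visit noise has SD 8, and values are held within 0 to 100. The log-odds of missing month 6 are −1.386 + s·(80 − adherence)/15, where s sets how strongly loss depends on low adherence.

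| s | Loss, control / SMS | Difference, everyone | Difference, completers | Shrinkage |
|---|---|---|---|---|
| 0 | 20.0% / 20.0% | 5.89 | 5.90 | none |
| 0.5 | 22.3% / 18.9% | 5.86 | 5.49 | 6% |
| 1.0 | 26.1% / 19.3% | 5.83 | 4.84 | 17% |
| 1.5 | 30.2% / 20.7% | 5.86 | 4.26 | 27% |

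The control mean among completers rises from 77.1 to 78.5, 80.1 and 81.6 as s increases from 0 to 0.5, 1.0 and 1.5. There is no bias when s = 0.

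**5. Effect on the adherence–cure analysis.** Assume average cure of 75%, the midpoint of the planned 65% and 85%, and that everyone lost is not cured.

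- Not cured: 288 × 0.25 = 72. Cured: 216.
- 20% loss: 288 − 230 = 58 lost, so 72 − 58 = 14 not-cured remain. Apparent cure is 216/230 = 94%.
- 10% loss: 288 − 259 = 29 lost, so 72 − 29 = 43 not-cured remain. Apparent cure is 216/259 = 83%.
- 30% loss: 288 − 202 = 86 lost, which exceeds 72, so the assumption cannot hold in full.

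The result is an upper bound on the distortion, because some transferred or lost patients will have been cured.

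**The case against.** The strongest reply is that the article does not say incomplete cases are dropped, and that a rule for partial VAS data may sit in a full protocol or analysis plan that is not shown. That is correct, and the absence of such a rule is not the point here. The point is the summary that is stated: both ways of completing it have a defect when loss is related to adherence.

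A reader might infer more than the documents support:

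- **That the t-test certainly compares only patients who stayed.** This holds for the literal three-value average. Table 1 can also be read as a t-test at each visit, and a month-2 test would not need month-6 attendance. Even so, the text names the average as the global measure.
- **That month-5 failures have no month-6 score.** The text says "If the smear test is negative, treatment continues during the sixth month" and classes month-5 positives as not cured. It does not say that their visits or VAS recording stop.
- **That the adherence–cure analysis conditions on the outcome and cannot be estimated.** The restriction is on retention, which is part of the outcome definition. A patient with three scores can still be smear-positive at month 6, and about 14 not-cured remain even in the 20% case above. The estimate would be imprecise and selective, but it exists.
- **That the arm difference must be biased toward zero.** That follows if low adherers are lost more often in the control arm; otherwise the direction is open. An example that gives all retained patients the same score in both arms shows zero difference by construction and proves nothing about size.

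It is also fair that appointment-keeping is a separate outcome in which those who do not come within the window are coded no, so missed visits are not wholly ignored. That does not repair the VAS measure.

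**Conclusion.** The concern holds in a limited form. The stated average and t-test give an arm comparison that depends on retention, or one that mixes treatment periods. With about 20% loss expected, the arm difference can be biased if loss is related to adherence and differs by arm. On the assumed inputs the shrinkage is 0% to 27%; the true size and direction cannot be derived from the documents. The adherence–cure analysis would also be restricted by retention, with up to about 58 of 72 not-cured participants lacking the full average at 20% loss. That count rests on 75% average cure and on every lost patient being uncured.

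The change is worth making because a better method is available on data already collected. It bears on a self-reported secondary outcome and an exploratory association, and leaves the primary test and the sample size as they are.

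**What to change.** 1. Replace the t-test on the three-visit average with a linear mixed model on all available VAS values, with terms for arm, visit, arm-by-visit and centre. Report the arm difference at each visit and averaged over visits.
2. Add a sensitivity analysis that assigns low adherence to visits missed through loss to follow-up. Do not apply it to transferred participants, since Cure status describes them as continuing treatment elsewhere.
3. For adherence versus cure, use VAS recorded before cure status is determined, for example at month 2, in all participants with that value. Report the result as an association.

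**Cost:** analysis wording and a little programming, with no new data. The model assumes that missingness is explained by the observed data, so it cannot recover a fall in adherence that was never reported; the sensitivity analysis is there for that reason. Month-2 VAS does not cover the continuation phase and still leaves out anyone absent at month 2.

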### Secondary objectives

The secondary objectives of this study are to evaluate the effect of sending SMS reminders on:

•Patient adherence to tuberculosis treatment (drug prescriptions collected and doses taken).

•The punctuality of appointments during the second, fifth and sixth months as well as whether appointments were kept.

•The number of treatment failures (KB positive patients at 5 months).

•The number of participants who develop resistance (as measured by Genexpert [33]).

•The degree of satisfaction of the participants.

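### The 'kept' variable duplicates 'prompt', and the punctuality classes leave out patients who never come, so neither appointment outcome isolates attendance

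*Protocol article*

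**What the plan says.** The Secondary objectives section of the protocol article lists, in one bullet, two things to be compared: "The punctuality of appointments during the second, fifth and sixth months as well as whether appointments were kept". Table 1 carries them as two separate outcomes, one binary and one categorical, each tested by chi-square.

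The Secondary outcomes section defines them as follows.

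- Binary variable: the answer 'yes' is given "for patients who come between 4 days before and 4 days after the appointment date". Every other patient is scored 'no'.
- Categorical variable: the label 'prompt' is used "for participants who come between 4 days before and 4 days after the appointment date". A patient who arrives before that window opens is 'early'. The remaining label, 'late', is reserved "for participants who come more than 4 days after the appointment date".

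No class is given for a patient who does not come. The article's rules for missing results (under Primary outcome and Plan for data analysis) concern cure status, and its intention-to-treat statement is made for the primary outcome.

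**The concern.** The objective asks a second question beyond punctuality: "as well as whether appointments were kept". A reader would expect the binary variable to answer it by separating patients who attended from those who did not. Instead it uses the window that defines 'prompt', so the two rows of Table 1 overlap and attendance as such is not isolated by either.

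The categorical variable has a different fault. Membership of any class depends on having come. If the reminders change who comes, the two arms' attenders are no longer comparable groups, and a chi-square among them can mix an effect on timing with an effect on attendance. At stake is the reading of a named secondary objective: an improvement in attendance could be diluted in one analysis and could look like worse punctuality in the other.

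**Working it through.** The plan gives no figure on this point, so the check is to run each possible attendance state through the stated definitions and then to see what can follow.

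**Step 1. Mapping (definitions from Secondary outcomes).**

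| What the patient does | Binary 'kept' | Punctuality class |
|---|---|---|
| Comes more than 4 days early | no | early |
| Comes within 4 days either side | yes | prompt |
| Comes more than 4 days late | no | late |
| Never comes | no | none |

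'Kept = yes' holds exactly when the class is 'prompt'. 'Kept = no' pools early attenders, late attenders and never-attenders. The last row has no punctuality class.

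**Step 2. Illustration A (all figures assumed, per 100 randomised at one visit, nobody early).** Control: 75 prompt, 10 late, 15 never. SMS: 75 prompt, 20 late, 5 never.

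- Attended at all: 75 + 10 = 85% against 75 + 20 = 95%. No-shows fall from 15% to 5%, by two thirds.
- 'Kept': 75/100 = 75% against 75/100 = 75%. No difference.
- 'Prompt' among patients with a class: 75/85 = 88.2% against 75/95 = 78.9%. The arm that kept more patients looks worse.
- If staff put no-shows under 'late' for want of another class: 10 + 15 = 25% against 20 + 5 = 25%. No difference.

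**Step 3. Illustration B (assumed).** Attendance is again 85% against 95%, but SMS attenders split between prompt and late in the control ratio, 75:10.

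- 'Kept': 75% against 95 × 75/85 = 83.8%, a difference of 8.8 points where attendance differs by 10.
- 'Prompt' among attenders: 75/85 = 88.2% in both arms. The punctuality test shows nothing.

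Under B the binary variable picks up most of the gain in attendance; under A it picks up none. In both, the punctuality test says nothing about attendance, and in A it points the other way. Which case is nearer the truth depends on how the additional attenders time their visits, which the documents do not say.

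**The case against.** **Counting an appointment as kept only if it falls near the date is a legitimate choice, and 'kept' is not blind to no-shows.** This stands in part. A no-show who becomes an on-time attender moves from 'no' to 'yes', as Illustration B shows. The flat result in Illustration A comes from holding 'prompt' at 75% and making all the additional attenders late. What remains is that the variable adds nothing to 'prompt' and does not isolate the attendance that the objective names separately.

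**The messages are about taking drugs, and dropout is seen elsewhere.** This is also fair. The Intervention group section describes no appointment reminder, the Cure status section defines loss to follow-up, and the primary analysis keeps such patients under best-case and worst-case scoring. The trial as a whole is not blind to dropout. The fault lies in these two secondary variables.

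Three stronger readings are tempting but not supported.

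- A reader might infer that both appointment analyses are restricted to attenders. The binary one is not: never-attenders are in it as 'no'.
- A reader might infer that the adherence score suffers in the same way, since the article says "We intend to use the average of the three values as a continuous variable to reflect patient global adherence to treatment". The text does not restrict that average to patients with all three values. A rule for missing visits in a secondary outcome may sit in an analysis plan that is not shown.
- A reader might take 20% as the plan's expected non-attendance. It is an inflation factor: 166 × 1.2 gives 199, which covers a loss of 33/199 = 16.6%. It is not a stated loss rate, still less a rate of missed appointments at each visit.

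**Conclusion.** The point holds as a fault of definition in two secondary outcomes. That 'kept' equals the indicator of 'prompt', and that never-attenders have no punctuality class, follows directly from the article's wording and needs no assumption. That the punctuality chi-square is then confined to a group selected after randomisation follows if the classes are applied as written.

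The size of the effect is not known. The 75% against 75% and the 88% against 79% rest wholly on assumed figures; they show that masking or reversal can happen, not that it is expected. The primary outcome and its sample size are unaffected. Because the keeping of appointments is a stated objective and the repair is cheap, the definitions should be corrected before the groups are compared.

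**What to change.** 1. Define 'kept' as attended at all by one pre-stated cut-off after the appointment date, the same in both arms. The next assessment visit would be too loose a cut-off, because the month 2 and month 5 visits are three months apart.
2. Analyse punctuality over all randomised patients in four classes: early, prompt, late, did not attend. The last class should use the same cut-off as item 1.
3. State how patients who have died or been transferred before an appointment are counted in both variables, so that they are not silently scored as no-shows or dropped.

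The cost is small: re-coding of the punctuality data that, according to Data collection, the secretary already gathers. This holds provided that actual visit dates, or at least non-attendance, are recorded, which the article does not say. If only the three classes were written down, the dates would have to be recovered from the follow-up files and health records. That must be done before the end of the study, when the Ethical considerations section has the health records destroyed.
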